### Component 2: health economic evaluation

Component 2 will use a decision analytic model to estimate the cost-efficiency of the OPEN AOS model intervention with standard care, taking into consideration the subsequent probability of presentation and re-presentation to the ED. The perspective for the analysis will be from the public hospital and health system.

This economic evaluation will be undertaken using retrospective data collected concurrently with Component 1, drawing on the same sample, time periods, and a sub-set of the routinely collected de-identified and linked data. The primary outcome will be the incremental expected cost per patient treated via OPEN AOS compared to standard care. Component 2 will follow the Consolidated Health Economic Evaluation Reporting Standards 2022 [54].Total annual cost of the OPEN AOS and additional ED equivalent capacity created will be based on forecast annual utilisation of OPEN AOS derived from historic utilisation estimates. An estimate of the net monetary benefit of the OPEN AOS model will be derived based on the annual utilisation of the OPEN AOS model multiplied by the incremental expected cost (saving) per person seen by the OPEN AOS model.

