## Methods

### Study aims

The aims of the OPEN AOS model evaluation are to:

Describe and compare the effectiveness and safety of the OPEN AOS model with standard ambulance attendance resulting in transport to ED care (standard care).Conduct an economic evaluation of the OPEN AOS model; and.Explore and understand the contextual factors influencing implementation to inform delivery and support potential scale and spread of the OPEN AOS model.

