## Control: standard ambulance model of care

In Queensland, prehospital emergency care is provided by the Queensland Ambulance Service (QAS), a single, state-wide, government-funded emergency ambulance service. Like other Australian and international ambulance services, primary triage of calls is completed by a non-clinical Emergency Medical Dispatcher to determine the nature and type of incident, and the response time criticality. All incidents are assigned as either: emergency (potentially life threatening – immediate response with lights and siren); urgent (acute – immediate response with no lights and siren); or non-emergency (time critical scheduled conveyance or routine) response. Incidents are subsequently assigned either an immediate dispatch response or are transferred for clinical review performed by a multidisciplinary team of experienced paramedics, medical practitioners, mental health clinicians, social workers and Registered Nurses (RNs). Following clinical review, patients are assigned the most appropriate health response, which may include a dispatch response or referral to equivalent care pathway, and/or virtual care (i.e., health care consultation provided via telehealth platform run by RNs and medical practitioners). The majority of QAS patients (over one million annually) are transported from the scene [38], and approximately 90.0% of transports are to public hospital EDs [39].

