### Inclusion criteria

Intervention: Adults aged 65 years or older who are permanent residents of RACFs situated within the MNHHS district geographical catchment area, with acute care needs and who were referred by the ambulance service to OPEN AOS between 08:00 and 20:00, Monday to Sunday, from 1 July 2022 to 30 June 2023. Patients can receive treatment by OPEN AOS on more than one occasion within the study period.

Control: Adults aged 65 years or older who are permanent residents of RACFs situated within the MNHHS district geographical catchment area, who received standard ambulance attendance and transport to a MNHHS ED between 08:00 and 20:00, Monday to Sunday, from 1 July 2022 to 30 June 2023. Only the first presentation for each patient within the study period will be examined.

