### Exclusion criteria

Patients were excluded if they (1) were assigned emergency status at primary (or secondary) triage (for any clinical reason); (2) did not reside in an RACF or resided in respite care; (3) were attended by ambulance and transported to ED care outside of OPEN AOS model operational hours (i.e. before 08:00 or after 20:00 Monday to Sunday); (4) were referred to OPEN AOS by any referrer other than ambulance services; or (5) received care outside the designated study period (1 July 2022 to 30 June 2023). (6) Patients included in the intervention group, i.e. those seen by OPEN AOS will be excluded from the control group.

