### Data collection and linkage

Patients living in RACFs are identified upon arrival to ED within EDIS^®^ and recorded as arriving by ambulance from a nursing home. Data extraction will occur retrospectively from state-based and MNHHS databases. An anonymous unique identifier (linkage ID) will be assigned to all cases by the Queensland Health Statistical Service Branch (SSB), enabling linkage of data from all sources (Table 1). These data provided to the researchers will not contain any key patient identifying features such as Unit Record Number (URN), name, address or Date of Birth (DOB). However, data such as age, postcode, and health facility will be included in the collection.

**Table 1 Tab1:** Data sources, date ranges and data descriptions for the OPEN AOS evaluation study

Data Source	Time Period	Data Description
RADAR Registry	1 Jul 2022 to 30 Jun 2023	OPEN AOS activity plus outcome data including: • outcomes of intervention • time stamps • clinician delegation Patient demographics for matching variables
Emergency Department Information System (EDIS^®^)	1 Jul 2022 to 28 Jul 2023	ED presentations of cohort members at one of the participating hospitals. • outcomes of intervention • time stamps Patient demographics and RACF address (presentation postcode and suburb) for matching variables
Metro North Health Funding and Data Insights	1 Jul 22 to 28 Jul 2023	Costs of initial ED presentations and subsequent re-presentations within 48 h and 28 days Patient unit record number for matching variables
Queensland Hospital Admitted Patient Data Collection	1 Jul 2020 to 30 Jun 2023	Patient co-morbidities identified during any hospital admission (using ICD-10-AM codes and ICD-10-AM code chapters), during the 24-month period preceding their presentations to the ED Patient demographics for matching variables
Death Registrations from the Registry of Births, Deaths and Marriages Queensland Cause of Death Unit Record File from the Australian Coordinating Registry	1 Jul 2022 to 02 Jul 2023	Death within 48 h of discharge from either emergency department presentation or OPEN AOS intervention Patient demographics for matching variables
RiskMan Queensland Health’s system for recording and managing clinical incidents, workplace events, consumer feedback, and risk	1 Jul 2022 to 02 Jul 2023	Patient Clinical Incident data within 48 h of discharge from the ED Patient demographics for matching variables

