### Data analysis

Costs include additional resources to deliver the new model of care (staffing and non-staffing costs) and downstream costs, such as ED presentation and ambulance transport re-deployment. ED costings will be based on an official average ED cost for the state of Queensland [55]. QAS costs will be based on average cost per ambulance incident for MNHHS over the study period [56]. Costs for the standard care will be based on the cost of QAS and ED presentation, considering subsequent ED re-presentation as provided from Component 1. As in component 1, all patient level data will be retrospectively sourced from existing routine data collection systems and linked by the state-based Statistical Services Branch. Uncertainty will be characterised using one way sensitivity analysis and probabilistic sensitivity analysis using Monte Carlo simulation [57, 58]. Furthermore, annualized cost, annual additional capacity created with respect to ED presentations avoided, and annual cost savings will be modelled for all 87 RACFs.

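### Component 2 makes ED attendance certain under standard care, and applies the resulting saving to OPEN AOS activity beyond the ambulance-referred patients in whom it is estimated

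*Protocol article*

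**What the plan says.** The Study aims define standard care by its outcome, an ambulance attendance that ended in ED transport. The Inclusion criteria accordingly admit as controls only residents "who received standard ambulance attendance and transport to a MNHHS ED between 08:00 and 20:00". The section Component 2: health economic evaluation uses the Component 1 sample, and its Data analysis states: "Costs for the standard care will be based on the cost of QAS and ED presentation", with later ED re-presentations added from Component 1.

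The section Control: standard ambulance model of care describes a wider pathway. After clinical review a patient receives a response "which may include a dispatch response or referral to equivalent care pathway, and/or virtual care", and the text says only that most ambulance patients are transported. The section on the OPEN AOS model adds that some of its patients are referred at secondary telephone triage, and that GPs, facility staff and other local teams also refer.

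The Exclusion criteria remove patients who "were referred to OPEN AOS by any referrer other than ambulance services". The annual net monetary benefit is then "the annual utilisation of the OPEN AOS model multiplied by the incremental expected cost (saving) per person seen by the OPEN AOS model", with utilisation forecast from historic use. Avoided ED presentations and savings are also modelled for all 87 facilities.

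On unit costs, Table 1 lists linked "Costs of initial ED presentations and subsequent re-presentations within 48 h and 28 days", while the Component 2 Data analysis says "ED costings will be based on an official average ED cost for the state of Queensland".

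**The concern.** A saving per patient treated by OPEN AOS needs an estimate of what would have happened to that patient without the service. The comparator answers a narrower question: what an episode costs once it has ended in ED. Patients enter it because they were transported, so it carries no information on how often a similar call would have ended elsewhere. This affects the primary outcome of Component 2, the incremental expected cost per patient, as well as the figure for ED presentations avoided.

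The second issue affects only the annual totals. A saving estimated in ambulance referrals is multiplied by a utilisation figure that, on a plain reading, covers every referral source. For a GP or facility referral, the ambulance use and ED attendance that the service replaces may differ, and the study does not estimate them.

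The protocol says that the findings will guide resource allocation, so both matter.

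**Working it through.** The protocol reports no Component 2 result to reproduce. Its one calculated figure, the Component 1 sample size, does reproduce (351 and 1053 give power 0.90), but has no bearing here.

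**Step 1: ED presentations avoided.** Let p be the probability of ED attendance under the standard pathway and q the probability under OPEN AOS. Avoided presentations per patient are p − q. The plan's structure gives 1 − q, so the overstatement factor is (1 − q)/(p − q).

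Inputs: the Samples section gives 735 OPEN AOS patients in the study year, with no referrer mix. Neither p nor q is given. I assume q = 0.10 and vary p.

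| p | Avoided, 735 × (p − 0.10) | Factor, 0.90/(p − 0.10) |
|---|---|---|
| 1.0 | 661.5 | 1.00 |
| 0.9 | 588.0 | 1.125 |
| 0.8 | 514.5 | 1.29 |
| 0.7 | 441.0 | 1.50 |
| 0.6 | 367.5 | 1.80 |

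With q = 0.20 the factors for p = 0.9, 0.8, 0.7 and 0.6 are 1.14, 1.33, 1.60 and 2.00.

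**Step 2: saving per patient.** Set the cost of ambulance plus ED to 1 and let a be the cost of OPEN AOS care on that scale (assumed; no unit costs are given). As a simplification, a contact that does not reach ED costs nothing. The saving is p − (a + q), and it is zero at p = a + q.

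| a (q = 0.10) | p = 1 | p = 0.9 | p = 0.8 | p = 0.7 | p = 0.6 |
|---|---|---|---|---|---|
| 0.5 | 0.40 | 0.30 | 0.20 | 0.10 | 0 |
| 0.7 | 0.20 | 0.10 | 0 | −0.10 | −0.20 |

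The simplification exaggerates the fall, because an attended but untransported contact still costs something. The table shows that the sign of the primary outcome can depend on p, not that it does.

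**Step 3: the multiplier.** Suppose 70% of utilisation is ambulance-referred with p = 0.8, and 30% comes from other referrers with p = p₀. Applying the ambulance-referred value to everyone gives 0.80 − 0.10 = 0.70 avoided per patient. The mixed value is 0.7 × 0.70 + 0.3 × (p₀ − 0.10).

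- p₀ = 0.5: 0.49 + 0.12 = 0.61, and 0.70/0.61 = 1.15. Against the plan's 0.90 the combined factor is 0.90/0.61 = 1.48.
- p₀ = 0.8: 0.49 + 0.21 = 0.70, so the multiplier adds no error.
- p₀ = 1.0: 0.49 + 0.27 = 0.76, and 0.70/0.76 = 0.92, an understatement.

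The direction of the multiplier error thus depends on p₀, which the protocol does not give.

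**The case against.** The comparator is declared openly, and comparing with transported episodes is a legitimate question. That stands for cost per transported episode. It does not carry over to presentations avoided or to savings among people who received OPEN AOS.

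The decision model is said to allow for the later chance of presenting and re-presenting to ED, and one-way and probabilistic sensitivity analyses are planned. An article may well leave their parameters to a fuller document. Even so, a sample made up only of transported patients cannot yield an index probability below 1, and simulation from its sampling variation leaves the value at 1. Only a deliberately chosen external value would change it, and nothing in the text commits to one.

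Several stronger readings are tempting, but the documents do not support them:

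- A reader might infer that the annual savings are the main output. The stated primary outcome is incremental cost per patient.
- A reader might infer that every error favours the service. For the multiplier this needs the unstated premise that other referrals had lower ED or ambulance use. Spreading fixed staffing cost over more patients could partly offset it, and the protocol does not say in terms that utilisation covers all referrers.
- A reader might infer that a state average ED cost hides differences in re-presentation. It does not: re-presentation frequency enters from Component 1, and only the cost per visit is flattened, in an unknown direction.
- A reader might fault the transport outcome for lacking a comparator. Component 1 defines it descriptively, for OPEN AOS patients only.

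**Conclusion.** The point holds in two parts of unequal strength.

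First, the index ED probability under standard care is fixed at 1 by how controls are selected and costed, against the protocol's own description of the pathway. The saving per patient and the presentations avoided are overstated whenever p is below 1. The protocol's statement that most ambulance patients are transported covers all its patients, not non-emergency calls from facilities, so it does not supply p. The overstatement of avoidance by 12.5% to 50% rests on assumed values (q = 0.10, p from 0.9 to 0.7). It shows how sensitive the result is and is not an estimate.

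Second, on the plain reading the saving is applied to referrals in which it was not estimated. Overstatement is likely if those patients would have used ambulance and ED less, but the documents do not establish this.

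The mismatch between linked ED costs and the state average is secondary: the two passages need reconciling, with no direction claimed.

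**What to change.** 1. Start the standard-care branch at ambulance contact, with an explicit probability of ED transport below 1. Inform it from eligible non-emergency facility incidents in the ambulance dispatch and clinical data already in the linkage, including those not transported, if they can be identified. The protocol identifies facility residents on arrival at ED, so this needs checking first.
2. Rates from the study period are themselves altered by diversion to OPEN AOS and are not a clean counterfactual. Vary the probability over a wide range in the one-way and probabilistic analyses, and report the value at which the saving becomes zero.
3. State which utilisation is multiplied. Use ambulance-referred activity for the main annual figure, and show other referrals as a separate scenario with its own counterfactual probability.
4. Reconcile Table 1 with the costing text, for example by reporting linked ED costs alongside the state average.

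The cost is a small additional extract of ambulance counts, some model wording and probably a less favourable headline saving.

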### Data analysis

Costs include additional resources to deliver the new model of care (staffing and non-staffing costs) and downstream costs, such as ED presentation and ambulance transport re-deployment. ED costings will be based on an official average ED cost for the state of Queensland [55]. QAS costs will be based on average cost per ambulance incident for MNHHS over the study period [56]. Costs for the standard care will be based on the cost of QAS and ED presentation, considering subsequent ED re-presentation as provided from Component 1. As in component 1, all patient level data will be retrospectively sourced from existing routine data collection systems and linked by the state-based Statistical Services Branch. Uncertainty will be characterised using one way sensitivity analysis and probabilistic sensitivity analysis using Monte Carlo simulation [57, 58]. Furthermore, annualized cost, annual additional capacity created with respect to ED presentations avoided, and annual cost savings will be modelled for all 87 RACFs.

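### Component 2 takes a public hospital and health-system perspective but gives inpatient stays no place in the cost comparison; the ED price source and the OPEN AOS index ambulance cost also need to be settled

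*Protocol article*

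**What the plan says.** All references are to the protocol article.

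- **Perspective and outcome** (Component 2: health economic evaluation). "The perspective for the analysis will be from the public hospital and health system". "The primary outcome will be the incremental expected cost per patient treated via OPEN AOS compared to standard care". The per-patient figure is then multiplied by annual utilisation to give a net monetary benefit, and the Data analysis section extends annual cost, capacity and savings to all 87 RACFs.
- **Modelled events** (same section). The decision model compares the two kinds of care "taking into consideration the subsequent probability of presentation and re-presentation to the ED".
- **Standard-care cost** (Data analysis under Component 2). "Costs for the standard care will be based on the cost of QAS and ED presentation, considering subsequent ED re-presentation".
- **OPEN AOS cost** (same section). The staffing and other resources of the service, plus "downstream costs, such as ED presentation and ambulance transport re-deployment". Ambulance costs use an average per incident for the district, in a sentence that is not tied to one group.
- **ED price** (same section). "ED costings will be based on an official average ED cost for the state of Queensland".
- **Data sources** (Data collection and linkage, Table 1). The Funding and Data Insights row supplies "Costs of initial ED presentations and subsequent re-presentations within 48 h and 28 days", together with the unit record number. The admitted-patient collection, 1 July 2020 to 30 June 2023, is listed for co-morbidities and matching demographics.

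**The concern.** A hospital-system perspective ordinarily includes the cost of admissions that follow the index episode. Every control patient reaches an ED by definition, and some OPEN AOS patients are also transported there, so admission can occur in both groups. The article itself treats admission as relevant. Its Background mentions iatrogenic complications in admitted RACF residents and names hospitalisation among the outcomes studied for outreach models.

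If admissions carry no cost, the primary economic outcome measures something narrower than the perspective announces. Any error per patient is then multiplied by annual utilisation and projected to 87 facilities.

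Two related uncertainties affect the same figure. The article extracts local ED costs but says it will price ED visits at a state average. It also names the ambulance cost explicitly for standard care only, although every study patient in the OPEN AOS group came through the ambulance service.

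**Working it through.** The article states no unit cost, admission rate or incremental cost, so there is no figure of its own to reproduce. The check sets the sections side by side and then sizes the gap with assumed inputs.

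**Step 1. Where could an admission enter?**

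| Element | What it covers | Inpatient stay included? |
|---|---|---|
| Model events | ED presentation, ED re-presentation | No |
| Standard-care cost | Ambulance, ED, repeat ED | No |
| OPEN AOS cost | Service resources, downstream items (open list) | Not named |
| Local cost extract (Table 1) | Index and repeat ED visits | No |
| Admitted-patient collection (Table 1) | Co-morbidities, matching demographics | Not for cost |

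Admissions are linked, but no row gives them a cost.

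**Step 2. Size of the inpatient omission.** The outcome is incremental, so what matters is the difference between groups:

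omitted saving per patient = (admission risk in control - admission risk in OPEN AOS) x cost of an admission.

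A positive value means the plan understates the saving from OPEN AOS; a negative value means it overstates it. In units of one average ED visit, all inputs assumed:

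| Risk difference | Admission = 2 ED visits | 5 ED visits | 10 ED visits |
|---|---|---|---|
| -0.05 | -0.1 | -0.25 | -0.5 |
| 0 | 0 | 0 | 0 |
| 0.2 | 0.4 | 1.0 | 2.0 |
| 0.5 | 1.0 | 2.5 | 5.0 |

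The range is -0.5 to +5.0 ED-visit equivalents per patient.

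**Step 3. Scaling.** The Samples section reports 735 patients treated by OPEN AOS in the 12-month study period. If that were the annual utilisation used, the range becomes 735 x (-0.5) = -367.5 to 735 x 5.0 = 3,675 ED-visit equivalents per year. This is illustrative only, because the plan uses a forecast of utilisation.

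**Step 4. ED price.** Table 1 obtains costs of index and repeat ED visits from the local health service. The Component 2 analysis text uses a Queensland average and gives the extracted local costs no role. The two sections name different sources for the same quantity.

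**Step 5. OPEN AOS ambulance cost.** The Inclusion and Exclusion criteria restrict the intervention group to ambulance referrals. The description of the OPEN AOS model says that these come either from paramedics at the facility or after telephone triage. The text does not say how this index contact is costed in the OPEN AOS group. If it were omitted, the understatement of OPEN AOS cost would be:

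share attended x cost of an ambulance incident.

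With assumed shares of 25% to 100% and an incident costing 0.5 to 1.5 ED visits, this is 0.25 x 0.5 = 0.125 to 1.0 x 1.5 = 1.5 ED-visit equivalents per OPEN AOS patient. A flat average per incident would also not distinguish telephone triage, attendance without transport, and attendance with transport.

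**The case against.** The strongest defence has four parts.

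**The downstream cost list is open-ended, and this is a condensed article.** Inpatient cost could fall under the open list, and Additional file 2, which explains outcomes for all components, is not shown. This leaves a little room. However, the standard-care sentence is a positive definition that stops at the ED, the modelled events are ED events only, and Table 1 gives admitted-patient data a different purpose. The open list does not repair that.

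**A state-average ED price fits a health-system perspective.** This stands. A reader might infer that the average contradicts the perspective, or that a single average prevents the Monte Carlo analysis from carrying uncertainty. The documents support neither. A probabilistic analysis places distributions on parameters, including mean unit costs. Nor does the article say which patients the official average covers. What remains is the unreconciled pair of sources.

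**The OPEN AOS ambulance cost is not excluded.** This also stands. A reader might infer that it is left out because it is named only for standard care. But the ambulance costing sentence is general, and re-deployment of ambulance transport is among the listed costs. The cost is unassigned.

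**The effect may be small or nil.** If admission risks are equal, the inpatient omission is zero. Multiplying an admitted share by a cost ratio in the control group alone would give a gross amount for one group, not the error in the incremental cost.

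**Conclusion.** The point holds for inpatient stays. As written, the plan yields an incremental cost of ambulance and ED care under a hospital-system label. The omitted term is about -0.5 to +5.0 ED-visit equivalents per patient under the assumed inputs. It can exceed the cost of an ED visit, can run in either direction, and vanishes if admission risks are equal.

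A reader might go further and conclude that the omission reverses the sign of the result. That cannot be shown: the article gives no base incremental cost, unit cost or admission rate.

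The ED price is a conflict between Table 1 and the analysis text, not a breach of perspective. The OPEN AOS ambulance cost is a gap in specification. All three should be settled before costs are analysed. The inpatient part matters most, because it alone decides whether the primary economic outcome matches its stated perspective.

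**What to change.** 1. **Inpatient costs.** Add the cost of admissions from the index episode and within 28 days, in both groups, and add admission to the model events. Use the already linked admitted-patient collection, extended from 30 June to 28 July 2023 to match the ED extract, and name an inpatient price source, which Table 1 lacks. Alternatively, restate the perspective and conclusions, including the net monetary benefit and the projection to 87 RACFs, as ambulance and ED costs only.
2. **ED price.** State the role of the local ED costs in Table 1 beside the Queensland average: use the local costs in the base case or in a sensitivity analysis.
3. **Ambulance cost.** State that the index ambulance contact is costed in the OPEN AOS group too, and how telephone triage, attendance without transport and attendance with transport are priced.

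The first option in item 1 costs one extract extension, one price source and some extra costing work. The alternative, and item 3's statement that the contact is costed, need only wording. Item 2 uses data already being extracted.
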